## Abstract

**Background:**

Although insight in schizophrenia spectrum disorders (SSD) has been associated with positive outcomes, the effect size of previous treatments on insight has been relatively small to date. The metacognitive basis of insight suggests that metacognitive training (MCT) may improve insight and clinical outcomes in SSD, although this remains to be established.

**Methods:**

This single-center, assessor-blind, parallel-group, randomised clinical trial (RCT) aims to investigate the efficacy of MCT for improving insight (primary outcome), including clinical and cognitive insight, which will be measured by the Schedule for Assessment of Insight (Expanded version) (SAI-E) and the Beck Cognitive Scale (BCIS), respectively, in (at least) *n* = 126 outpatients with SSD at three points in time: i) at baseline (T0); ii) after treatment (T1) and iii) at 1-year follow-up (T2). SSD patients receiving MCT and controls attending a non-intervention support group will be compared on insight level changes and several clinical and cognitive secondary outcomes at T1 and T2, whilst adjusting for baseline data. Ecological momentary assessment (EMA) will be piloted to assess functioning in a subsample of participants.

**Discussion:**

To the best of our knowledge, this will be the first RCT testing the effect of group MCT on multiple insight dimensions (as primary outcome) in a sample of unselected patients with SSD, including several secondary outcomes of clinical relevance, namely symptom severity, functioning, which will also be evaluated with EMA, hospitalizations and suicidal behaviour.

**Trial registration:**

ClinicalTrials.gov: NCT04104347. Date of registration: 26/09/2019 (Retrospectively registered).

## Background

Schizophrenia and related disorders remain associated with relatively poor psychosocial outcomes [1]. Impaired insight has been reported to be the strongest predictor of this poor outcome in psychotic disorders [2]. However, the effect size of previous treatments on insight changes in psychotic disorders has been relatively small to date [3, 4], which may have been the result of not tackling the actual underpinnings of insight in psychosis.

Several theories have been proposed to explain what underlies ‘lack of insight’ in schizophrenia spectrum disorders. First, lack of insight could be viewed as having a function in terms of being protective or preserving self-esteem, i.e., a denial mechanism [5]. Second, lack of insight may also be considered as a primary symptom of the disorder [6]. Third, the neurocognitive basis of insight was in part supported by a meta-analysis [7], which also suggested that other variables, namely metacognition, which was defined as ‘the ability to think of one’s and others’ thinking’ [8, 9], may affect insight. Indeed, patients with schizophrenia have been reported to show metacognitive deficits [10, 11] and poorer metacognitive performance is linked with impaired insight in schizophrenia [12]. Metacognitive training (MCT) may therefore improve insight, which should also have a positive impact on clinical outcomes.

MCT was first developed by Steffen Moritz and Todd Woodward [13] and is available at no cost at: http://www.uke.de/mct. Since then, one systematic review [14] and four meta-analyses [15–18] have replicated the positive effects of MCT on positive symptoms, particularly delusions, when compared with ‘treatment as usual’ (TAU), although one meta-analysis [19] failed to show such an association. However, to the best of our knowledge no definitive randomised clinical trial (RCT) using MCT has considered insight as primary outcome to date, although three previous RCTs found other non-MCT metacognitively oriented therapies to improve insight in first-episode psychosis [20] and schizophrenia [21, 22].

Clinical and cognitive insight are different, albeit related, concepts [2, 12]. There has been a growing interest in clinical insight in psychosis since the multidimensional model of insight proposed by David [23], which encompasses three different, albeit overlapping, dimensions - illness recognition, symptom relabelling and treatment compliance – and has been consistently replicated ever since [24]. Multidimensional measurement scales, such as the Scale of Unawareness of Mental Disorder (SUMD) [25] and the Schedule for Assessment of Insight (SAI-E) [26], were also devised for research. Cognitive insight is a core metacognitive domain which refers to the person’s ability to evaluate and correct his/her own distorted beliefs and misinterpretations (self-reflectiveness) and the tendency to overconfidence in one’s conclusions (self-certainty) [10].

The ***main aim*** of this RCT is to test whether MCT can improve insight, including clinical and cognitive insight, in patients with schizophrenia over a 1-year follow-up. As ***secondary aims,*** we will investigate the effect of MCT-related insight changes on clinical outcomes, including symptomatic severity, hospitalizations, suicidal behaviour and psychosocial functioning. In addition, we will pilot the use of ecological momentary assessment (EMA) via two web-based applications - www.MEmind.net [27] and the Evidence-Based Behaviour platform eB2 app [28] - to measure functioning in a subsample of participants.

Specifically, the following five hypotheses are to be tested: i) that MCT will result in higher cognitive and clinical insight levels and that MCT-induced insight improvement will be linked with ii) reduced symptom severity and iii) hospitalizations, iv) lower suicide rates and v) better functioning than in controls.

## Methods

### Study design

This is a single-center, assessor-blind, parallel group, two-armed randomised controlled trial (RCT) over a 1-year follow-up period. Participants will be assessed at baseline (T0), following which they will be randomised to either group MCT (experimental group) or a support group (control group) and they will be reassessed after treatment, i.e., at approximately 8 weeks (T1), and at 1-year follow-up (T2).

The study protocol has been approved by the local Research Ethics Committee of the Instituto de Investigación Sanitaria (IIS)-Fundación Jiménez Díaz (Madrid, Spain), from which patients will be recruited as detailed below, and registered as RCT-EC044-19_FJD_HRJC. Also, the protocol is registered at ClinicalTrials.gov (NCT04104347).

### Sample and eligibility criteria

The sample comes from the Centro de Salud Mental de Arganzuela, which is an outpatient clinic linked with Hospital Universitario Fundación Jiménez Díaz (FJD), which provides publicly-funded medical and mental healthcare to approximately 500,000 inhabitants residing in our geographic catchment area in Madrid (Spain). Those adults (age 18–64 years) with a confirmed diagnosis of psychosis according to the Mini International Neuropsychiatric Interview, 5th Edition (MINI) [29], will be invited to participate in the study. The exclusion criteria will be as follows:
IQ ≤ 70 as measured by the short form of the Wechsler Adults Intelligence Scale (WAIS)-IV [30].History of head injury and/or a neurological condition.Having received a metacognitively oriented therapy within the previous year.Low level of Spanish.Lack of cooperativeness with the assessment and/or “intervention”.

Therefore, the initial recruitment is unselected, that is, all adults (age 18–64 years, both inclusive) with a confirmed diagnosis of schizophrenia spectrum disorder receiving mental healthcare in our outpatient clinic (hence, clinically stable – i.e., not acutely unwell -) could be included in the study, provided they do not meet any of the above exclusion criteria. This approach has, of course, advantages and disadvantages, which are discussed further in the section of discussion. Those who agree to take part in the study will be asked to give written informed consent.

### Recruitment process

Recruitment will occur at the outpatient clinic known as Centro de Salud Mental de Arganzuela at which two consultant psychiatrists ([name], [name]) and one consultant psychologist ([name]) will refer potential candidates to the principal investigator of the project ([name]) to arrange a first pre-recruitment interview during which the relevant information of the project is explained to the candidate in lay terms, including an information leaflet. Those agreeing to participate in the study are screened against the above inclusion/exclusion criteria at this point. Those who are found to fulfill the study selection criteria undertake a neurocognitive assessment. Specifically, the WAIS-IV [30] is administered by a MSc-level clinical psychologist ([name]) in order to rule out an IQ ≤ 70, which is an exclusion criterion. Those with an IQ > 70 are administered the Trail Making Test (TMT) [31], which assesses executive function and has been found to correlate with insight scores in psychosis patients [32], by [name] shortly after the WAIS-IV in order to complete the baseline neurocognitive assessment at this point.

After a short break of around 5 min, [name] performs the MINI [29] to confirm the diagnosis of psychosis and conducts the psychopathological, insight, metacognitive and functioning assessments detailed below. Also, a set of demographic and clinical variables, which are listed below, are collected at this baseline interview.

All participants will be encouraged to continue taking medication as prescribed by the treating consultant psychiatrist, usually antipsychotics, and to receive non-metacognitive oriented psychotherapy, such as psychoeducation. There will be no restrictions on medication changes over the trial, which can be made by the treating consultant at any time, although medication-related variables will be considered in secondary analyses as potential mediators/confounders. Participants are informed of their right to drop out of the study at any time without having to disclose a specific reason, which will have no implications on treatment or service provision. Participants are not compensated with any amount of money for completing the assessments and/or receiving the interventions, namely MCT or attending a weekly support group.

### Randomisation and assessor-blindness

After the baseline (T0) assessment participants are randomised to either MCT or the support group, both of which are run by [name] and [name], through a computerized plan (no stratification factors) in blocks of 10 subjects (maximum number of each group) and assessor ([name])-patient blind. Only one co-principal investigator of the project ([name]) has access to the randomisation plan, but the assessor ([name]) is not informed of the patient’s allocation group, thus ensuring assessor-blindness since the patient may find out what intervention he/she is receiving, for which the study cannot be considered to be double-blind, although it is ‘single-blind’, that is, ‘assessor-blind’. Also, big efforts will be made on the ground to reduce the risk that the assessor ([name]) may become accidentally unblinded and patients are reminded that they should not disclose their group assignment at any time. At the end of the baseline assessment, participants receive an envelope with the intervention assignment from an independent administrator who is not involved in the research team. A reminder mobile text-message is also sent to participants within the next 24 h with the group details (date, time and venue), which is also re-sent again during the 24 h prior to the appointment, which is very similar to our routine clinical practice. Hence, assessor-blindness is guaranteed at all times throughout the study period since the assessor ([name]) is not involved in the randomization plan or the active interventions. See the CONSORT flowchart in Fig. 1, below, for details.

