#### Power calculations and estimation of sample size

Given that the mean SAI-E score for psychosis patients is 13/28 with a standard deviation of around 6 [32, 35], a difference of 2 points (e.g., 13 vs. 15) between groups (e.g., MCT vs. controls), which is considered to be clinically meaningful [26], is equivalent to an effect size of 0.33 with a two-tailed alpha significant level set at 5%. Under these assumptions, for reaching a sufficient statistical power of β = 80% at the end of the study, we will need *n* = 63 subjects in each arm, that is, a total sample size of *N* = 126 patients, who will be analysed at the end of the study on an intention-to-treat (ITT) basis. Attrition rates in previous RCTs investigating MCT effects on symptoms were low (approximately 10%) [18]. However, since we will follow-up patients over a more prolonged period (1 year) we have conservatively assumed a much higher drop-out rate of 50%. Under this assumption, the study will be carried out with an initial sample size of *N* = 252 patients, i.e., *n* = 126 participants in each group/arm at the study inception, which will also allow both ITT and ‘per protocol’ analyses with sufficient power. See the CONSORT flow chart in Fig. 1 for details.

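### A single fixed and published block size of 10 in one clinic lets anyone who can follow all earlier allocations deduce up to about one in six; undisclosed mixed block sizes would largely remove this at little cost

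*Protocol article*

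**What the plan says.** The section Randomisation and assessor-blindness states that patients are randomised after the baseline assessment "through a computerized plan (no stratification factors) in blocks of 10 subjects (maximum number of each group"). No other block size is mentioned. Study design describes one site: "This is a single-center, assessor-blind, parallel group, two-armed randomised controlled trial (RCT) over a 1-year follow-up period".

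The randomisation section also lists safeguards. Only one co-principal investigator can see the list. An administrator from outside the research team hands over the assignment in an envelope after baseline. The assessor is not told the arm, and patients are asked not to reveal it. The same section says that two therapists run both kinds of group. It explains that the trial cannot be called double-blind "since the patient may find out what intervention he/she is receiving".

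Under Recruitment process, two psychiatrists and one psychologist of the same clinic "will refer potential candidates to the principal investigator". Consent, screening and baseline testing follow, and then allocation. Under Sample and eligibility criteria, patients can be excluded for poor cooperation.

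**The concern.** With one list and one known block size, past allocations carry information about future ones. Once one arm of a block is full, the remaining places are determined. Restricting access to the list and using envelopes hides future entries from direct view. It does not prevent deduction from entries already used.

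Referral, screening and the judgement of cooperativeness all come before allocation, so a prediction could influence who enters and when. The article's own discussion (Strengths and weaknesses) links lower cooperativeness with poorer insight, which is the primary outcome. Selection at that step would act on something tied to the endpoint, and the planned ANCOVA adjusts only for measured baseline data.

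**Working it through.** The article gives no predictability figure, so there is none to reproduce.

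**Inputs**
- Block size 10, no strata (Randomisation and assessor-blindness); one centre (Study design).
- Planned enrolment 252, that is 126 per arm (Power calculations and estimation of sample size).
- Ratio within a block: not stated. A 5:5 split is an assumption drawn from the equal arms.
- Observer: assumed to know the block size, the block boundaries and every earlier allocation in order.

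**Certain allocations, block of 10.** For a balanced block of 2m patients, the expected number of forced allocations is 2m/(m + 1), a share of 1/(m + 1).
- m = 5: 10/6 = 1.67 per block, share 1/6 = 16.7%. Enumerating all C(10,5) = 252 orderings gives the same result. (That this equals the planned enrolment is a coincidence.)
- The last place in a block is always forced. In 55.6% of blocks only that one is forced, and in 44.4% two or more are.
- 252 patients are 25 full blocks plus 2: 25 × 1.67 = 41.7, and 41.7/252 = 16.5%.

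**Certain allocations, block of 20.** The words "in blocks of 10 subjects (maximum number of each group") could also mean 10 per arm.
- m = 10: 20/11 = 1.82 per block, share 1/11 = 9.1%.

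**Best guess.** Always guessing the arm that lags gives m + (2^(2m)/C(2m,m) − 1)/2 correct guesses per block.
- m = 5: 5 + (1024/252 − 1)/2 = 6.53 of 10, or 65.3%, against 50% by chance.
- m = 10: 61.7%.

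**Mixed block sizes.** This was simulated with 200 runs of 252 patients. The observer knows the set of possible sizes but not the sequence, and updates by Bayes' rule.

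| Block sizes | Certain | Best guess correct |
|---|---|---|
| 10, fixed | 16.6% | 65.2% |
| 8, 10, 12 | 1.3% | 65.1% |
| 6, 8, 10 | 1.5% | 66.3% |
| 4, 6, 8 | 2.0% | 68.1% |

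**Imbalance.** The arms can differ by at most half the largest block: 10/2 = 5 now, and 12/2 = 6 with sizes 8, 10 and 12.

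**The case against.** A fixed block of 10 is an accepted design, and several points tell against a strong reading.

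- **Open label.** A reader might infer an open-label trial. The article says assessor-blind. Therapists and patients learn the arm, but the assessor is not told it. This objection stands.
- **Known to recruiters.** A reader might infer that one allocation in six is in fact known before randomisation. That requires the full ordered history and the block boundaries. Nothing in the article gives the three referrers that history. Names are removed, so it cannot be checked whether a referrer is also a therapist. This stands, and it makes the figures upper bounds.
- **Pace of enrolment.** The article plans 252 patients in a 6-month enrolment period. At 26 weeks that is 252/26 = 9.7 a week, so a block of 10 is used up in about a week, while sessions are weekly. Attendance would show little of a block before it closes, and it does not show the order. This stands at the planned rate and weakens if accrual is slower.
- **Steering is hard.** An interview, consent, screening and a long baseline battery lie between referral and envelope, and three clinicians feed one list. Timing a referral is not timing an allocation. This limits the risk without removing it.
- **Adjustment.** Insight is measured before allocation by the blinded assessor and is adjusted for. Only unmeasured differences would remain.
- **The parenthesis.** A reader might call it an error, because a balanced block of 10 puts 5 in each arm. It may instead describe therapy-group capacity, which two such blocks would fill. It is ambiguous, not wrong.
- **Limited remedy.** Mixing block sizes hardly changes the best-guess rate. This is true: the gain is confined to certain allocations.

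**Conclusion.** The point holds as a minor one. The article fixes and publishes a single unstratified block size for one clinic in which the therapists of both arms, and the patients, come to know the allocations. The listed safeguards do not prevent deduction from past entries.

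The size is at most about one allocation in six (1.67 per block, about 42 of 252) if blocks are 5:5, or about one in 11 if the block is 20. Both figures assume an observer with the complete ordered history and the block boundaries; for anyone else the share is about 0. The article does not show that any referring clinician is such an observer, so it supports no claim that allocation will be subverted. What remains is an avoidable weakness in a stated rule, and an unclear definition of the block.

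**What to change.** Generate the list, or its remaining blocks if enrolment has begun, with randomly mixed block sizes, for example 8, 10 and 12. Do not disclose the sizes to referrers, therapists or the assessor. In the protocol, describe them only as randomly varying blocks. Replace the parenthesis with a separate statement of therapy-group capacity, and fill the groups from the randomised queue up to that number.

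The cost is regenerating the list, plus a momentary arm imbalance of up to 6 instead of 5. The gain is a fall in certain allocations from about 17% to about 1%. The best-guess rate stays near 65%, so the existing concealment steps are still needed.

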**Fig. 1 Fig1:**
[figure not shown]
Study CONSORT chart. Estimated flow of participants over the trial period

### Assessments

Participants will be assessed at three timepoints: i) T0: at baseline; ii) T1: after treatment; iii) T2: at 1-year follow-up. Data on different variables will be collected at each of these assessments, which is detailed in the SPIRIT flowchart shown in Table 1, below.

**Table 1 Tab1:**
[figure not shown]
SPIRIT flowchart

*MCT* Metacognitive Training*. PSE* Psychoeducation. *MINI* Mini International Neuropsychiatric Interview, 5th Edition [29]. *WAIS* Wechsler Adult Intelligence Scale [30]. *TMT* Trail Making Test [31]. *BCIS* Beck Cognitive Insight Scale (BCIS) [10]. *SAI-E* Schedule for Assessment of Insight, expanded version [26]. *PANSS* Positive and Negative Syndrome Scale [38, 39]. *CDSS* Calgary Depression Scale for Schizophrenia [41]. *GAF* General Assessment of Functioning [42]. *WHODAS* World Health Organization Disability Schedule [43]. *SLDS* Satisfaction Life Domains Scale [44]. *PAS* Premorbid Adjustment Scale [47]. *ERTF* Emotional Recognition Test Faces [51]

Both raters ([name] and [name]) completed a rater-training workshop and received individual training in which they were observed as they assessed pilot patients by using the project scales explained below under the supervision of a senior consultant psychiatrist with expertise in the use of these instruments ([name]).

### Outcome measures

#### Co-primary outcomes

Insight is the primary outcome of this RCT and both clinical and cognitive insight will be considered.
*Clinical insight* will be measured with the Spanish version [33] of the Schedule for Assessment of Insight, expanded version (SAI-E) [26]. The SAI-E takes the form of a semi-structured interview which enquires about different aspects of insight and provides scores on three insight dimensions in line with David’s model [23] - illness recognition, symptom relabeling, treatment compliance - and a total insight score. The scale was found to be easily applicable in routine clinical practice [34] and good to excellent inter-rater reliability was reached, with total insight scores intra-class correlations coefficients ranging from 0.92 to 0.98 (*p* < 0.001) [35]. [name] received training from the scale author ([name]) and they both co-led the validation study of the SAI-E Spanish version [33], which will be used in this RCT.*Cognitive insight* will be assessed by the Spanish version [36] of the Beck Cognitive Insight Scale (BCIS) [10], which is a 15-item self-administered scale which evaluates self-reflectiveness (9 items) and self-certainty (6 items). A composite index can thus be calculated by subtracting self-certainty from self-reflectiveness. Internal consistency was found to be acceptable (Cronbach’s α = 0.60–0.68) [37].

#### Secondary outcomes

Secondary outcomes of this investigation include symptomatic severity, hospitalizations, suicidal behaviour, metacognition, neurocognition and functioning.

##### Symptomatic severity

Symptoms severity will be rated with the Spanish version [38] of the Positive and Negative Syndrome Scale (PANSS) [39]. Based on a systematic review of previous PANSS factor analyses [40], five symptomatic dimensions will be analysed: positive, negative, disorganization, mania and depression, which will also be measured with the Calgary Depression Scale for Schizophrenia (CDSS) [41].

##### Hospitalizations

Number of hospitalizations*,* i.e., time to hospitalization (i.e., survival analyses, see statistical analyses below), and total number of days in hospital will be considered. Mental health presentations to the emergency department will be included in secondary analyses.

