### Statistical analysis

Participants’ data will be analysed at the end of the study on an intention-to-treat (ITT) basis, thus including all patients with baseline information available. Imputation methods will be used to estimate missing values. All the analyses will be performed with the Statistical Package for Social Science version 25.0 (SPSS Inc., Chicago, IL, USA).

First, demographic and clinical characteristics of groups (MCT and controls), including insight measures, will be compared at baseline so parametric and non-parametric tests will be used as appropriate. Also, for descriptive purposes, between-arm completion rates differences will be analysed at the end of the study.

Second, in order to investigate the primary outcome of the study, namely insight changes over the trial period, univariate analysis of covariance (ANCOVA) models will examine between-group differences (MCT and controls) in the SAI-E and BCIS total and subtotal scores changes from T0 to T1 and from T0 to T2 (as the dependent variable), whilst adjusting for baseline data. Hence, the effects of treatment (independent of time) and treatment group allocation*time interactions on insight changes will be investigated. We will also explore within-group scores changes between T0, T1 and T2. Specifically, we will estimate effect sizes (Cohen’s *d*) and the corresponding 95% confidence intervals (CI) from the imputed datasets for between- and within-group insight scores changes. In accordance with Cohen’s conventions [52], effect sizes will be classified as ‘small’ (*d < 0.2),* ‘medium’ *(d* = 0.2–0.5) or ‘large’ (*d* > 0.8). Due to multiple testing and the subsequent risk of type I error, results will be adjusted using Bonferroni correction.

Third, for the secondary outcomes evaluated with continuous variables, i.e., symptom severity (PANSS and CDSS) and functioning (GAF, SDLS and WHODAS), analogous ANCOVA models will be used. For those binary secondary outcomes, namely suicidal behaviour and readmissions, survival analyses, i.e., multivariable Cox regression models [53], will model time to the outcome event (i.e., first suicidal event or hospital admission, respectively) or the censoring date as appropriate, whilst adjusting for baseline variables.

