### Outcome measures

In addition to the primary outcome of this RCT, namely insight, we will consider several clinical outcomes, both positive and negative, such as symptom severity, functioning, readmissions and suicidal behaviour, thus testing the so-called ‘Insight Paradox’ [54]. Although the positive impact of MCT on symptoms has been established [14–18], most of previous RCTs included in these meta-analyses compared MCT with TAU. Therefore, not only this RCT may replicate this, but also by comparing the MCT group with an active intervention control group, if the above positive effect was shown, this would provide further support for the benefits of MCT on symptoms. Beyond and above the effects of MCT on symptoms, functioning will be comprehensively examined, consistently with current guidelines focused on recovery as main outcome measure [55]. Also, functioning will be evaluated with novel methodology such as EMA, which has not been sufficiently researched in psychosis patients.

However, insight was also linked with negative outcomes. In particular, insight was thought to lead to depression, hopelessness and suicidality, which is known as the demoralization syndrome [56, 57] or ‘Insight Paradox’ [54]. However, recent research did not show a ‘direct’ relationship between insight and suicidality in first-episode psychosis, which was due to the confounding effects of previous suicide attempts and depression on such an association [32]. The question therefore arises, i.e., whether an insight improving intervention (such as MCT, which is to be tested in this trial) may reduce suicide risk (and improve mood) in psychosis, which will be properly investigated in this RCT. In addition to suicidal behaviour-related outcomes, we will test whether MCT can reduce admissions over the trial period, which is of relevance from a cost-effectiveness perspective [58].

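### Number of hospitalizations is treated as time to hospitalization and modelled only up to one admission, so repeat admissions do not enter the stated analysis

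*Protocol article*

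**What the plan says.** **Outcome definition (Protocol article, Methods, Secondary outcomes, Hospitalizations).** The sentence opens with the number of hospitalizations and goes straight on: "i.e., time to hospitalization (i.e., survival analyses, see statistical analyses below), and total number of days in hospital will be considered". The first two terms are joined as if one restated the other. Days in hospital is added as a further measure.

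**Model (Methods, Statistical analysis).** The route for admissions is: "For those binary secondary outcomes, namely suicidal behaviour and readmissions, survival analyses, i.e., multivariable Cox regression models". These models "will model time to the outcome event (i.e., first suicidal event or hospital admission, respectively) or the censoring date as appropriate". The other route, ANCOVA, is given "for the secondary outcomes evaluated with continuous variables, i.e., symptom severity (PANSS and CDSS) and functioning (GAF, SDLS and WHODAS". The path analysis at the end of the section covers mediators, moderators and confounders of the associations already described.

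**What the result is meant to show.** In Background, the hypothesis is that "MCT-induced insight improvement will be linked with ii) reduced symptom severity and iii) hospitalizations". In the Discussion, under Outcome measures: "we will test whether MCT can reduce admissions over the trial period, which is of relevance from a cost-effectiveness perspective". The design is a "two-armed randomised controlled trial (RCT) over a 1-year follow-up period", with group sessions over the first 8 weeks or so.

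**The concern.** The number of admissions in a year and the time until an admission are different endpoints. They need different models and can give different answers. Here the second takes the place of the first, both in the outcome definition and in the analysis.

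The question in the Discussion is whether admissions fall over the trial period. A model that stops at one admission per patient answers part of that: whether patients are admitted at all, and how soon. It says nothing about whether those who are admitted come back. Time to first admission could show no difference while repeat admissions fall in one arm, or could favour MCT while the total does not change.

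Timing adds to this. Treatment takes about 8 weeks, so a patient first admitted during the course leaves the risk set before finishing it. Any later effect on that patient's admissions is then invisible to the model.

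There is also a reporting risk. With two quantities under one label, the report could call either of them the hospitalization result after the data are seen.

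**Working it through.** There is no hospitalization figure to reproduce. The protocol gives no admission rate, hazard ratio or expected number of events, and its only sample-size calculation is for the SAI-E. The check is therefore a comparison of sections.

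1. **What is named.** Hospitalizations names three things: number of hospitalizations, time to hospitalization and days in hospital. The first two are presented as one.

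2. **What has a model.** Statistical analysis calls readmission binary and models time to the event or to censoring. On the natural reading, the word *first* covers both the suicidal event and the hospital admission. If it covers only the suicidal event, the result is the same: a standard Cox model for a binary outcome uses one event per patient.

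3. **What that does to repeat admissions.** Take two patients first admitted on the same date, one with no further admission and one with three more. Their counts are 1 and 4. Their contributions to the Cox model are identical, apart from covariates.

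4. **Whether another analysis picks them up.** No count or recurrent-event model is described. The ANCOVA models are for scale scores. The path analysis works on the associations already set out and adds no count outcome.

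5. **What the claims need.** The Discussion's question about admissions over the trial period is a comparison between arms that depends on how many admissions occur. The Background hypothesis is different: it links hospitalizations to improvement in insight brought about by MCT, which is a question of mediation.

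Steps 1 to 4 show that a named secondary outcome, the number of hospitalizations, has no stated analysis that uses its repeat events. Step 5 shows that the Discussion's claim relies on that outcome.

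**The case against.** **Time to first admission is a legitimate endpoint.** This stands. Leaving out later events is a property of every time-to-first-event analysis and is not an error in itself. The fault is presenting it as the number of hospitalizations. Nothing in the documents requires it to be demoted.

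**A condensed article leaves detail to a fuller plan.** This stands in part. A fuller plan could add models. It would not remove the equation of count with time in the outcome definition, or the one-event model, both of which the article states.

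Four stronger readings are tempting, and the documents do not support them.

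- *Days in hospital will go unanalysed.* A reader might infer this because days are missing from the list of continuous outcomes. That list is not complete: metacognition and neurocognition are named secondary outcomes and are missing from it too. The protocol says days will be considered, and the method may sit in a plan not shown.
- *A given share of admissions is lost.* The share beyond the first is 1 − P(at least one)/mean. If the mean is assumed to be 0.2 per patient-year with no clustering (Poisson), P(at least one) = 1 − exp(−0.2) = 0.181, and the share is 1 − 0.181/0.2 = 9%. If the mean is assumed to be 0.8 with negative binomial dispersion 3, P(at least one) = 1 − (1 + 3 × 0.8)^(−1/3) = 0.335, and the share is 1 − 0.335/0.8 = 58%. None of these inputs comes from the protocol, which recruits clinically stable outpatients. The share also measures neither bias nor loss of power.
- *A cost-effectiveness analysis is undermined.* None is promised. The Discussion only calls the question relevant from that perspective.
- *A comparison of admission counts between arms would test hypothesis iii.* It would not. That hypothesis concerns change through insight, and a comparison of arms contains no insight term.

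**Conclusion.** The concern holds in limited form. The protocol treats the number of hospitalizations and time to hospitalization as one outcome and models only one admission per patient. Repeat admissions therefore do not enter the stated analysis of a named secondary outcome, and the Discussion's question about reduced admissions is only partly addressed.

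This rests on the wording of the article alone and on no assumed rate. For the same reason, no size can be put on the loss.

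The weight is moderate. The co-primary insight outcomes, the sample size, randomisation and data collection are untouched. What is affected is what the trial can say about admissions.

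**What to change.** In Hospitalizations and in Statistical analysis:

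- List number of admissions, time to first admission and total days in hospital as three separate measures.
- Keep Cox regression for time to first admission.
- Add a between-arm negative binomial model for the number of admissions over the year, with log follow-up time as offset. Use the number of previous admissions as covariate; it is already among the baseline variables under Demographic and clinical data. The offset allows for unequal follow-up, which matters in a trial that plans for 50% drop-out.
- Compare total days between arms with a method suited to skewed data with many zeros. The ANCOVA of change from T0 does not carry over naturally, because days in hospital accrue after randomisation.
- State in advance which of the three supports the Discussion's claim about reduced admissions.
- Leave the insight-mediated part of hypothesis iii to the path analysis, and say so.

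The cost is revised wording and a small amount of extra analysis. The data are already planned, and recruitment, visits and interventions do not change.
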